# Protocol for a multi-centered, stepped wedge, cluster randomized controlled trial of the de-adoption of oral chlorhexidine prophylaxis and implementation of an oral care bundle for mechanically ventilated critically ill patients: the CHORAL study

**DOI:** 10.1186/s13063-019-3673-0

**Published:** 2019-10-24

**Keywords:** Chlorhexidine, Critical care, Ventilator-associated pneumonia, Oral care, Stepped-wedge cluster randomized controlled trial, Process evaluation, Mechanical ventilation

## Abstract

**Background:**

Routine application of chlorhexidine oral rinse is recommended to reduce risk of ventilator-associated pneumonia (VAP) in mechanically ventilated patients. Recent reappraisal of the evidence from two meta-analyses suggests chlorhexidine may cause excess mortality in non-cardiac surgery patients and does not reduce VAP. Mechanisms for possible excess mortality are unclear. The CHORAL study will evaluate the impact of de-adopting chlorhexidine and implementing an oral care bundle (excluding chlorhexidine) on mortality, infection-related ventilator-associated complications (IVACs), and oral health status.

**Methods:**

The CHORAL study is a stepped wedge, cluster randomized controlled trial in six academic intensive care units (ICUs) in Toronto, Canada. Clusters (ICU) will be randomly allocated to six sequential steps over a 14-month period to de-adopt oral chlorhexidine and implement a standardized oral care bundle (oral assessment, tooth brushing, moisturization, and secretion removal). On study commencement, all clusters begin with a control period in which the standard of care is oral chlorhexidine. Clusters then begin crossover from control to intervention every 2 months according to the randomization schedule. Participants include all mechanically ventilated adults eligible to receive the standardized oral care bundle. The primary outcome is ICU mortality; secondary outcomes are IVACs and oral health status. We will determine demographics, antibiotic usage, mortality, and IVAC rates from a validated local ICU clinical registry. With six clusters and 50 ventilated patients on average each month per cluster, we estimate that 4200 patients provide 80% power after accounting for intracluster correlation to detect an absolute reduction in mortality of 5.5%. We will analyze our primary outcome of mortality using a generalized linear mixed model adjusting for time to account for secular trends. We will conduct a process evaluation to determine intervention fidelity and to inform interpretation of the trial results.

**Discussion:**

The CHORAL study will inform understanding of the effectiveness of de-adoption of oral chlorhexidine and implementation of a standardized oral care bundle for decreasing ICU mortality and IVAC rates while improving oral health status. Our process evaluation will inform clinicians and decision makers about intervention delivery to support future de-adoption if justified by trial results.

**Trial registration:**

ClinicalTrials.gov, NCT03382730. Registered on December 26, 2017.

**Electronic supplementary material:**

The online version of this article (10.1186/s13063-019-3673-0) contains supplementary material, which is available to authorized users.

## Background

Ventilator-associated pneumonia (VAP) was previously considered to have high morbidity and mortality and was the target for prevention strategies [1]. Evidence-based guidelines encouraged ICUs to adopt “ventilator bundles”, including the application of chlorhexidine gluconate mouth rinse, to prevent VAP [2–4]. However, two updated meta-analyses suggest chlorhexidine may cause excess mortality in some critically ill patients whilst failing to prevent VAP [5, 6]. Moreover, recent analyses demonstrate that the attributable mortality for VAP is low (1%) [7]. In combination, these data have placed guidelines for the use of oral care with chlorhexidine into question.

A variety of mechanisms have been proposed for the lack of effect of chlorhexidine oral rinse on VAP [8–11]. However, the biological mechanism for chlorhexidine causing excess mortality is less clear. Chlorhexidine could be directly toxic or it may trigger hypersensitivity reactions contributing to erosive mucosal lesions, predisposing patients to infection and respiratory failure [12, 13]. The additional burden of such complications in critically ill patients could negatively impact mortality.

Safe and effective oral care plays a critical role in the oral and systemic health outcomes of millions of people admitted to intensive care units (ICUs) worldwide each year for invasive mechanical ventilation [14]. Inadequate salivary flow associated with critical illness and oral intubation cause oral health dysfunction, including abnormal oropharyngeal colonization with bacteria [15, 16]. Aspiration of this abnormal oral bacteria leads to infection-related ventilator-associated complications (IVACs), which ultimately increase the duration of mechanical ventilation and costs of treatment [17]. Furthermore, resultant xerostomia is associated with severe pain and discomfort [18, 19].

With evidence for a lack of benefit in VAP prevention, as well as possible harm, immediate discontinuation of oral chlorhexidine in the ICU is a possible solution. However, the lack of a clear mechanism for harm, low to moderate quality of the evidence contributing to recent meta-analyses, and the potential for unintended consequences of rapid and widespread de-adoption all necessitate evaluation through scientifically rigorous de-adoption [20]. Therefore, we will conduct a multi-centered, stepped wedge, cluster randomized controlled trial (SW-CRT) of the de-adoption of oral chlorhexidine and implementation of a standardized oral care bundle in critically ill patients undergoing mechanical ventilation with an embedded process evaluation.

### Research questions

What are the effects of the de-adoption of oral chlorhexidine and introduction of a standardized oral care bundle on mortality in mechanically ventilated critically ill adults?What are the effects of the de-adoption of oral chlorhexidine and introduction of a standardized oral care bundle on IVAC rates and oral health dysfunction scores in mechanically ventilated critically ill adults?

## Methods/design

### Design

The CHORAL study is a SW-CRT. Each cluster (defined as a single ICU) will be randomly allocated to receive the intervention according to a staggered implementation schedule in one of six sequential steps comprising 2-month intervals. There will be six clusters in total with all clusters commencing with a 2-month control period (baseline) in which standard of care includes chlorhexidine oral care for IVAC prevention. Each cluster will maintain chlorhexidine oral care until they are allocated to crossover from control to intervention according to the randomization schedule. The study completes with a 2-month period during which all clusters have fully de-adopted chlorhexidine and implemented the standardized oral care bundle. Total study duration will be 14 months (Fig. 1). We follow CONSORT cluster trial extension guidelines for SW-RCTs in the design of this study [21]. The SPIRIT checklist is provided in Additional file 2.

**Fig. 1 Fig1:**
[figure not shown]
Stepped-wedge schedule of the CHORAL study. Clusters sequentially cross over from control phase to intervention phase. Observational data collection is depicted during control (*plus sign*) and intervention (*asterisks*) periods

The key rationale for our selection of a SW-CRT design includes: (1) avoidance of contamination of the intervention for control participants that is a risk with individual patient randomization; (2) provision of the intervention education at the cluster level; (3) intention to leave the oral care intervention in place at study end; and (4) measurement of outcomes at the level of both clusters and individual patients.

A mixed-methods process evaluation will be conducted as an adjunct to the main trial. Guided by a framework for process evaluation of complex interventions in cluster randomized trials, we will study the processes supporting implementation of our intervention. The objective of our process evaluation is to provide a clear description of implementation processes and to facilitate understanding of the main trial results [22].

### Study setting and participants

The CHORAL study will be conducted in six adult ICUs in five university-affiliated hospitals in Toronto, Canada.

### Inclusion and exclusion criteria

#### Unit inclusion for SW-CRT

We approached units meeting the following criteria for participation: (1) adult ICU capable of providing invasive mechanical ventilation; (2) existing intention to de-adopt oral chlorhexidine prophylaxis; (3) contribution of patient demographic, treatment, and outcome data to the Toronto Intensive Care Observational Registry (iCORE); and (4) admission of at least 50 ventilated patients per month. Exclusion criteria: units not meeting inclusion criteria.

#### Patient inclusion criteria for SW-CRT

All adult patients who receive invasive mechanical ventilation in the participating ICUs and are able to receive standardized oral care can be included. For mortality and IVAC rates we will exclude those patients who start in the control group and cross-over to the intervention group.

### Randomization and allocation concealment

Randomization of ICUs to the six sequential steps will be computer-generated by the study statistician. Each ICU will be randomly allocated to start the study intervention according to the randomized staggered implementation schedule and the sequence will be concealed until interventions are assigned. Clusters agreed to participate with the understanding that order of allocation to the intervention would be unknown in advance of randomization. Within control and intervention periods, random dates of observation at each site will be computer generated to collect oral health dysfunction scores and establish intervention fidelity in a subset of patients.

### Blinding

This is a non-blinded study. Clinical and study staff cannot be blinded to study allocation due to the nature of the intervention. Clinical staff in all clusters will be provided with initial education regarding the study intervention and ongoing education to reinforce delivery of the standardized oral care bundle. Independent iCORE assessors of mortality and IVAC outcome data will be blinded.

### Pre-intervention phase

#### Oral care observations

In the 2 months preceding de-adoption of chlorhexidine and introduction of a standardized oral care bundle at each site, a trained standardized assessor will use structured observational tools to document baseline oral care delivery, including chlorhexidine concentration and application method [23]. We will document pain presence (yes/no) during oral care using the Critical-Care Pain Observation Tool (CPOT; range 0–8, score > 2 indicating pain) [24], and oral health dysfunction using the Beck Oral Assessment Scale (BOAS) [25] on randomly selected dates. The CPOT was recently validated for detecting pain presence in non-verbal ICU patients during oral care delivery and the BOAS tool has been previously validated in the ICU population [26]. For patients able to self-report (mouth words, nod, point), we will also measure symptom intensity using a 0–10 intensity-rating scale for (i) oropharyngeal dryness and (ii) procedural oral pain [27] immediately following the oral care delivery. We aim to observe a minimum of 25 patients in each ICU during this baseline phase (150 total).

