### Intervention phase

Four weeks prior to the intervention phase, an investigator or designate will deliver intensive education targeting clinician knowledge, attitudes, and behaviors regarding the new oral care intervention to ICU cluster leads using a train-the-trainer model [28]. Cluster leads will comprise an ICU physician-nurse (or physician-pharmacist) dyad supported by unit-level oral care nurse champions. We will utilize an integrated knowledge translation (iKT) approach to facilitate practice change, including an iKT oral care tool kit supporting our oral care intervention [29] comprising a detailed oral care protocol (Table 1), touchpoint video (an edited video of ICU patient experiences and recommendations for oral care), and expert video instruction on oral care delivery (Additional file 1). To minimize bias, cluster leads will distribute the iKT oral care tool kit to frontline ICU nursing and allied health staff 2 weeks prior to the intervention phase.

**Table 1 Tab1:** Oral care bundle

Comprehensive oral care Q12 hours	Equipment	Procedure
1. Oral assessment	•Flashlight •Tongue depressor •Gloves •Face shield	•Explain procedure to patient •Gently open mouth or use mouth prop •Inquire about mouth/throat pain (0–10 NRS) •Use CPOT tool to evaluate pain in non-verbal pt. •Treat pain prior to proceeding
2. Tooth brushing	•Yankauer •12 or 14 French flexible catheter •Small soft-bristle or suction toothbrush •Sponge swabs •Sterile water •Gloves •Face shield	•Explain procedure to patient •Perform hand hygiene •Elevate HOB 30–45 degrees as tolerated •Use oral prop to open mouth as needed •Oral suction with Yankauer or sterile flexible catheter to remove secretions that may migrate down airway •Moisten toothbrush with sterile water •Connect suction toothbrush to continuous suction if applicable •Brush accessible teeth and gums for 2 full minutes or 30 s per quadrant; brush in one continuous line LUQ > RUQ > RLQ > LLQ •Gently brush tongue
3. Mouth and lip moisturizer	•Swabs •Mouth moisturizer/saliva replacement or sterile water •Gloves •Face shield	•Explain procedure to patient •Use oral prop to open mouth as needed •Use 1–3 swabs to apply moisturizer to oral mucosa, tongue, and lips
4. Deep oral suctioning	•Yankauer or flexible catheter •Gloves •Face shield	•Explain procedure to patient •Use oral prop to open mouth as needed •Deep oropharyngeal suction (above the cuff) to remove pooled secretions

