Maintenance oral care Q4 hours and PRN	Equipment	Procedure
Mouth and lip moisturizer	•As above	•As above
Oral secretion removal	•As above	•As above

*CPOT* Critical-Care Pain Observational Tool, *HOB* head of bed, *PRN* pro re nata or “as needed”

The following oral care interventions will commence in the intervention phase for each step and become standard of care:
Intervention 1 (oral chlorhexidine de-adoption): Each cluster will de-adopt oral chlorhexidine from routine practice for all invasively ventilated patients. Use of routine oral chlorhexidine will not be permitted during the intervention period with the exception of patients prescribed chlorhexidine for non-standard care.Intervention 2 (oral care protocol): This two-part, nurse-led intervention incorporates comprehensive and maintenance oral care activities. Comprehensive care involves twice daily (morning and evening) a) oral assessment (inspection of the oral space, teeth and gums); b) tooth brushing; c) oral/lip moisturization; and d) suctioning oropharyngeal secretions above the cuff. Maintenance care involves, at a minimum of every 4 h and as needed, a) oral/lip moisturization; and b) suctioning oropharyngeal secretions above the cuff (Table 1).

One month after allocation to the intervention, a trained assessor will begin to observe fidelity of delivery of the oral care protocol and assess patient oral health status using the BOAS, CPOT, and patient self-report of oral health symptom intensity on randomly selected dates. We will provide each cluster lead with written feedback on these observations for dissemination to frontline ICU staff. For sites identified as having low intervention fidelity during audits (< 70% compliance across all bundle components), we will provide additional education and intensified audit frequency. We estimate observing a minimum of 25 patients in each ICU during the intervention phase (150 total).

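### Baseline oral-care observations are not kept out of the two weeks in which frontline staff already hold the new protocol, which leaves the BOAS and fidelity contrasts open to dilution

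*Protocol article*

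**What the plan says.** **Baseline window.** The protocol article, under Oral care observations, places the baseline measurements directly before each ICU's switch: "In the 2 months preceding de-adoption of chlorhexidine and introduction of a standardized oral care bundle at each site, a trained standardized assessor" documents oral care delivery, CPOT pain, BOAS and, where patients can report, dryness and procedural pain. The target is at least 25 patients per ICU, 150 in all. The section on pre- and post-intervention oral care fidelity uses the same two months for the fidelity data. Under Randomization and allocation concealment, the observation dates are computer-generated at random within the control and intervention periods.

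**Preparation of staff.** The Intervention phase section puts two activities inside that window. First: "Four weeks prior to the intervention phase, an investigator or designate will deliver intensive education targeting clinician knowledge, attitudes, and behaviors". This is given "regarding the new oral care intervention to ICU cluster leads using a train-the-trainer model". Second, "cluster leads will distribute the iKT oral care tool kit to frontline ICU nursing and allied health staff 2 weeks prior to the intervention phase". The kit is described as "comprising a detailed oral care protocol (Table 1), touchpoint video" and an expert instruction video.

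**Formal start.** The same section says: "The following oral care interventions will commence in the intervention phase for each step and become standard of care". The Design section has each cluster stay on chlorhexidine until its crossover. After the switch, observation of fidelity, BOAS, CPOT and symptoms waits one month.

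**Analysis.** BOAS is compared in a linear mixed model with treatment phase as the independent variable. CPOT, self-reported symptoms and fidelity are compared between the two phases with Wilcoxon rank sum tests.

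**The concern.** The nurses who receive the kit are the people whose oral care is being observed, and the kit tells them how to brush, moisturise and suction under the new bundle. If some begin before the formal start, late baseline observations no longer describe usual care, yet the two-phase comparisons count them as control. The article allows for a transition on one side only: a month's gap after the switch and none before it.

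Early uptake would lower (improve) baseline BOAS and raise baseline fidelity. Both changes shrink the before-after difference. At stake are a named secondary outcome, the pain and symptom comparisons, and the process evaluation's account of how far practice changed.

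**Working it through.** **Inputs**
- Window: 2 months, taken as 61 days (8.7 weeks); the range 59 to 62 days changes little.
- Tool-kit exposure: the last 14 days (Intervention phase).
- Sample: 25 per ICU, 150 per phase (Oral care observations; Sample size).
- BOAS: SD 2, target difference 2 points, design effect 3.5 to 10, stated power 80% (Sample size, Oral health dysfunction).
- Assumptions not in the document: two-sided alpha 0.05; dates spread evenly over the window; early uptake *u* of 25% to 50% of the full effect during the two weeks.

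**1. The plan's own figure.** Effective n per phase = 150/DEFF, and power = Φ(δ / (SD·√(2/n)) − 1.96).
- DEFF 10: n = 15; 2 / (2·√(2/15)) = 2.74; 2.74 − 1.96 = 0.78; power about 78%. This is close to the stated 80%.
- DEFF 3.5: n = 42.9; 4.63 − 1.96 = 2.67; power about 99.6%.

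The stated power therefore corresponds to the upper end of the design-effect range.

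**2. Share of baseline observations after tool-kit distribution.** 14/61 = 23% (23% to 24% over 59 to 62 days). 25 × 0.23 = about 6 per ICU; 150 × 0.23 = about 34.

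**3. Dilution of a true two-point difference.** Observed difference = 2 × (1 − 0.23·u).

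| Uptake *u* (assumed) | Shift in baseline mean | Observed difference | Power, DEFF 10 | Power, DEFF 3.5 |
|---|---|---|---|---|
| 0 | 0 | 2.00 | 78% | 99.6% |
| 25% | 0.11 to 0.12 | 1.89 | 73% | 99% |
| 50% | 0.23 | 1.77 | 68% | 98% |

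The shift is about 0.06 to 0.12 SD, or 6% to 12% of the target difference.

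**4. After the change.** With 25 patients per ICU all observed before tool-kit distribution, power returns to the first row. If the exposed observations are instead dropped and not replaced, 150 − 34 = about 116 baseline patients remain. With the same design effects, power is then about 72% (DEFF 10) or 99% (DEFF 3.5).

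**5. Feasibility.** 61 − 14 = 47 days remain. At the unit entry criterion of at least 50 ventilated patients a month, that is about 50 × 47/30.5 = 77 patients per ICU, of whom 25 are needed.

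**The case against.** The strongest reply is that holding a protocol is not the same as delivering it. The bundle formally starts only at the switch, and chlorhexidine continues until then. Staff must be prepared before a dated crossover, and the article presents the two-week timing as a step against bias. Observers also record oral care delivery during baseline, so late drift could be examined. All of this stands as a limit on the claim: the exposure is certain, the uptake is not. None of it separates the exposed dates from the unexposed ones, and the window itself is stated, not left to a document that is not shown.

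A reader might go further in three ways that the document does not support.

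- **Counting all four weeks as exposed** (28/61 = 46%, about 69 of 150). The education four weeks ahead goes to cluster leads, and four weeks is when it is delivered, not a period of changed bedside care.
- **Assuming full uptake before launch.** The article waits a month after the switch before observing, and plans extra education for sites below 70% compliance, so it does not expect instant uptake even then.
- **Extending the point to mortality and IVAC.** Those outcomes use all control time: (1+2+…+6) × 2 = 42 cluster-months. The six two-week windows are about 84/(42 × 30.4) = 6.6% of it, and chlorhexidine is still in use. A sensitivity analysis there is ordinary content for an analysis plan that is not shown.

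One further objection has force. The BOAS model as described has no calendar-time term, so moving baseline dates earlier slightly widens an unadjusted gap between phases.

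**Conclusion.** The point holds as an unguarded risk to the observed oral-care outcomes: BOAS, CPOT, self-reported symptoms and fidelity. About 23% of baseline observations would be made after frontline staff have the new protocol and would be analysed as control. The likely direction is toward no difference.

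The size is modest: a loss of about 0.11 to 0.23 of two BOAS points. In power it matters only near the upper design effect, which is the one that matches the stated 80%. These figures rest on evenly spread dates, the assumed 25% to 50% uptake and two-sided alpha 0.05. The document does not show that the baseline data are in fact contaminated. This is a low-cost improvement to a secondary outcome and the process evaluation, not a threat to the primary analysis.

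**What to change.** Generate the random baseline dates only from the part of the two-month window before tool-kit distribution, roughly the first six to seven weeks, and keep 25 patients per ICU. State this restriction under Oral care observations and in the fidelity section.

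If the dates can no longer change, which the end date of March 31, 2019 under Trial status suggests, repeat the BOAS and fidelity comparisons without baseline observations from the last two weeks and report both results. The same can be done for CPOT and symptoms.

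**Cost.** One restriction in the date generator and a sentence of text. The 25 patients must be observed in about 6 to 7 weeks instead of 8.7. Patient numbers allow this, but the article does not give the assessors' capacity. The calendar gap between phases widens slightly. The fallback costs some precision, with about 116 baseline patients instead of 150.
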